# Sacubitril/valsartan versus valsartan in regressing myocardial fibrosis in hypertension: a prospective, randomized, open-label, blinded endpoint clinical trial protocol

**DOI:** 10.3389/fcvm.2023.1248468

**Published:** 2023-08-22

**Keywords:** myocardial fibrosis, sacubitril/valsartan, ARNi, hypertensive heart disease, heart failure, cardiovascular magnetic resonance imaging, biomarkers

## Abstract

**Background:**

Diffuse interstitial myocardial fibrosis is a key common pathological manifestation in hypertensive heart disease (HHD) progressing to heart failure (HF). Angiotensin receptor–neprilysin inhibitors (ARNi), now a front-line treatment for HF, confer benefits independent of blood pressure, signifying a multifactorial mode of action beyond hemodynamic regulation. We aim to test the hypothesis that compared with angiotensin II receptor blockade (ARB) alone, ARNi is more effective in regressing diffuse interstitial myocardial fibrosis in HHD.

**Methods:**

Role of ARNi in Ventricular Remodeling in Hypertensive LVH (REVERSE-LVH) is a prospective, randomized, open-label, blinded endpoint (PROBE) clinical trial. Adults with hypertension and left ventricular hypertrophy (LVH) according to Asian sex- and age-specific thresholds on cardiovascular magnetic resonance (CMR) imaging are randomized to treatment with either sacubitril/valsartan (an ARNi) or valsartan (an ARB) in 1:1 ratio for a duration of 52 weeks, at the end of which a repeat CMR is performed to assess differential changes from baseline between the two groups. The primary endpoint is the change in CMR-derived diffuse interstitial fibrosis volume. Secondary endpoints include changes in CMR-derived left ventricular mass, volumes, and functional parameters. Serum samples are collected and stored to assess the effects of ARNi, compared with ARB, on circulating biomarkers of cardiac remodeling. The endpoints will be analyzed with reference to the corresponding baseline parameters to evaluate the therapeutic effect of sacubitril/valsartan vs. valsartan.

**Discussion:**

REVERSE-LVH will examine the anti-fibrotic potential of sacubitril/valsartan and will offer mechanistic insights into the clinical benefits of sacubitril/valsartan in hypertension in relation to cardiac remodeling. Advancing the knowledge of the pathophysiology of HHD will consolidate effective risk stratification and personalized treatment through a multimodal manner integrating complementary CMR and biomarkers into the conventional care approach.

**Clinical Trial Registration**: ClinicalTrials.gov, identifier, NCT03553810.

## Introduction

1.

Hypertensive heart disease (HHD) is manifested in a range of cardiac morphological and functional derangements including the development of left ventricular hypertrophy (LVH). Beyond structural compensation (increased LV wall thickening and LV mass) due to hemodynamic effects of sustained elevated blood pressure, a complex interplay between co-morbidities and neurohormonal status appears to contribute to the maladaptive progression, leading to cardiomyocyte hypertrophy, cell death, alterations in the coronary microcirculation, and diffuse interstitial fibrosis (1–3). These changes eventually lead to LV dysfunction and potentially to overt heart failure (HF). Thus, pharmacological therapies fostering regression of myocardial fibrosis play a vital role as a beneficial intervention for HHD.

Conventional anti-hypertensive therapies which suppress the renin–angiotensin–aldosterone system (RAAS) including angiotensin-converting enzyme inhibitors (ACEi) or angiotensin receptor blockers (ARB) have been shown to regress myocardial fibrosis on biopsy (4, 5).

Angiotensin receptor–neprilysin inhibitor (ARNi) is a new class of drug that blocks the RAAS and augments natriuretic peptides. It is a dual agent comprising a neprilysin inhibitor (sacubitril) and an ARB (valsartan). Sacubitril/valsartan has shown superior benefits over conventional ARB or ACEi monotherapy in terms of blood pressure lowering (6), clinical outcome improvement (7), and reduction in cardiac wall stress and injury biomarkers (8–10) and is endorsed in international guidelines for the treatment of HF (11, 12). Pre-clinical data has suggested that sacubitril/valsartan has superior efficacy in promoting the regression of myocardial fibrosis compared with valsartan alone in HF with diabetes (13).

In patients with hypertension, a 52-week treatment with sacubitril/valsartan has demonstrated a greater reduction in LV mass, measured by cardiovascular magnetic resonance (CMR), compared with the ARB olmesartan (14). Importantly, this reduction in LV mass appears to be independent of changes in blood pressure. Similarly, ventricular remodeling regression irrespective of blood pressure control was observed in perimenopausal women treated with sacubitril/valsartan for 24 weeks who showed greater reduction in indexed LV mass on echocardiography, compared with those on valsartan. The accompanying reduction of fibrosis-related serum biomarkers (TGF-β, CT-GF, and α-SMA) suggested the possible involvement of fibrosis in cardiac remodeling (15). Therefore, direct examination of therapy-effected regression of fibrosis on CMR imaging, along with existing evidence, would consolidate the role of fibrosis in myocardial remodeling and its modulation by ARNi.

In REVERSE-LVH, we aim to compare the changes in diffuse interstitial myocardial fibrosis with respect to LVH regression in HHD patients undergoing sacubitril/valsartan vs. valsartan treatment alone. We hypothesize that 52 weeks of sacubitril/valsartan therapy will result in greater regression of diffuse interstitial myocardial fibrosis and LV mass relative to valsartan therapy, independent of blood pressure control. With the advances of CMR, diffuse interstitial myocardial fibrosis can now be measured non-invasively using T1 mapping and extracellular volume (ECV) quantification (16).

## Methods

2.

### Study design and population

2.1.

REVERSE-LVH is a prospective, randomized, open-label, blinded endpoint (PROBE) clinical trial, designed to compare the effects of 52 weeks of treatment with sacubitril/valsartan (an ARNi class drug) with valsartan (an ARB class drug) on the primary endpoint of change in interstitial volume measured by CMR in patients with hypertension and LVH. The secondary endpoints include changes in LV mass, volumes, and function measured by CMR from baseline.

Patients with hypertension and LVH diagnosed according to age- and sex-specific CMR thresholds in Asians (17) are eligible. Participants who were previously recruited to the REMODEL study (our ongoing prospective study that examines myocardial fibrosis in hypertension; ClinicalTrials.gov Identifier: NCT02670031) are screened for eligibility. This cohort consists of participants from community clinics and two major tertiary heart centers in Singapore: National Heart Centre Singapore (NHCS) and National University Heart Centre, Singapore (NUHCS). No restrictions based on ethnicity or gender are imposed. Details of the inclusion and exclusion criteria are listed in Table 1. Written informed consent is obtained from all participants. Informed consent, randomization, all study visits, and procedures are carried out at NHCS.

**Table 1 T1:** Inclusion and exclusion criteria.

Inclusion criteria
1. Age ≥21 years of age
2. Physician diagnosed essential hypertension, on at least one medication for blood pressure control (including newly diagnosed hypertension or resistant hypertension)
3. Increased LV mass on CMR (based on local age- and sex-specific CMR ranges)
Exclusion criteria
1. Known secondary causes of hypertension
2. Other causes of LVH (such as hypertrophic and infiltrative cardiomyopathy)
3. Previous intolerance to ARB
4. History of heart failure
5. History of cardiovascular events (myocardial infarction, strokes, and transient ischemic attacks)
6. Known atrial fibrillation
7. History or presence of any other disease with a life expectancy of <3 years
8. Stage IV/V chronic renal disease (eGFR of <30 mL/min/1.73 m^2^)
9. Serum potassium of >5.2 mmol/L (mEq/L) at visit 1
10. Unable to commit to study follow-up
11. Unable to understand or comply with study procedures (including CMR)
12. Pregnant or nursing (lactating) women

ARB, angiotensin II receptor blocker; CMR, cardiovascular magnetic resonance; eGFR, estimated glomerular filtration rate; LV, left ventricular; LVH, left ventricular hypertrophy.

### Randomization, blinding, and treatment

2.2.

To eliminate possible confounding or residual effects from RAAS suppression by anti-hypertensive medications that some participants might be taking at the time of enrollment, participants who are on ACEi or ARB will undergo a 2-week washout period prior to commencing their respective assigned therapies. This duration of washout period is consistent with ARNi studies (6, 18) and is more than five elimination half-lives of commonly used ACEi and ARB (19, 20). Alternative therapies or up-titration of other anti-hypertensive agents (including but not limited to amlodipine and/or hydrochlorothiazide) are prescribed to control blood pressure during the 2-week washout period (Figure 1).

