**Figure 1 F1:**
[figure not shown]
Recruitment, randomization, and treatment protocol. ACEi, angiotensin-converting enzyme inhibitor; ARB, angiotensin II receptor blocker; LV, left ventricular; LVH, left ventricular hypertrophy; Δ, change.

Participants are randomized on an allocation ratio of 1:1 to either sacubitril/valsartan or valsartan without blinding. Randomization service is provided by the Singapore Clinical Research Institute (SCRI) in closed, opaque, and sequentially numbered envelopes. Research member who measures CMR endpoints is blinded to treatment allocation and clinical details including blood pressure values.

The treatment duration is 52 weeks, with the same target systolic blood pressure for both treatment groups which is less than 140 mmHg according to contemporary guidelines at the time of study conception (21, 22). The initial dosage of sacubitril/valsartan is 100 mg–200 mg/day and can be titrated up to a maximum dose of 400 mg/day. The initial dosage of valsartan is 80 mg–160 mg/day and can be titrated to a maximum dose of 320 mg/day. Medications are titrated to the maximum dose tolerated by the participants. If the study medications are inadequate for optimal blood pressure control, additional non-RAAS inhibiting anti-hypertensive agents are prescribed. Study medications are dispensed by a pharmacist at NHCS. Treatment compliance is monitored by pill counting at each clinic visit.

Participants may withdraw from the study at any time. Withdrawal can be initiated and documented by the investigator if continuation would be detrimental to the participant’s well-being. If withdrawal happens after more than 12 weeks of randomized treatment, all endpoint investigations will be performed at the time of withdrawal (unless participant is not contactable, refused, or deceased). The first participant was recruited on 19 June 2019.

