### Study procedures

2.3.

The study is organized into five scheduled clinic visits and two phone calls as outlined in Table 2. Additional visits are arranged if necessary. At baseline visit, demographics (age, sex, race), past medical history, and anthropometric measurements (height, weight) are collected. The EuroQol EQ-5D-3L questionnaire is used to evaluate five aspects of health-related quality of life (mobility, self-care, usual activities, pain/discomfort, and anxiety/depression) at baseline, visit 4 and visit 5.

**Table 2 T2:** Study visits and procedures.

Visit	Washout	1	2	3		4		5
Week	−2	0	4^a^	8^a^	12^a^	26^a^	38^a^	52
Informed consent taking	×^b^	×^b^			Phone call follow-up		Phone call follow-up	
Demographics and anthropometrics collection	×^b^	×^b^						
Collection of past medical history, including medications	×^b^	×^b^						
Urine pregnancy test	×	×	×	×		×		×
Randomization		×						
Health-related quality of life assessment		×				×		×
Study medication dispense		×	×	×		×		
Medication adherence check		×	×	×		×		×
Blood collection for renal function and potassium level		×	×	×		×		×
Blood collection for hematocrit		×						×
Blood collection for storage		×						×
Office blood pressure measurement		×	×	×		×		×
24-h ambulatory blood pressure monitoring		×	×	×		×		×
Cardiovascular magnetic resonance		×						×
Adverse events evaluation		×	×	×		×		×

^a^
Additional clinic visits are arranged if necessary.

^b^
These procedures are only done once, either at the washout visit or visit 1.

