#### Sample size calculation

2.4.1.

We determined that a sample size of 35 participants per group would provide the trial with 80% power at a 5% significance level (two-sided) to detect an absolute minimum difference between treatment groups of 3.5 mL/m^2^ in terms of change in interstitial volume from baseline following 52 weeks, assuming an SD of 5.8 mL/m^2^ [data that was subsequently published (25)] and a moderate correlation of 0.60 between interstitial volumes at baseline and 1 year. The effect size was based on an estimate of the magnitude of myocardial fibrosis regression that could be expected to translate into improved clinical outcomes (5). The study plan is to randomize 80 participants, allowing up to 15% dropout and treatment discontinuation.

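### The two-week washout shows that prior ACEi/ARB is cleared, not that its effect on fibrosis is gone; pre-specify ANCOVA in place of optional, significance-triggered adjustment (minor)

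*Protocol article*

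**What the plan says.** **Washout (protocol article, section 2.2).** The text says that "participants who are on ACEi or ARB will undergo a 2-week washout period prior to commencing their respective assigned therapies". The aim is "To eliminate possible confounding or residual effects from RAAS suppression" by antihypertensives that participants may be taking when they enrol. Two reasons are given for the length: it matches other ARNi studies, and it "is more than five elimination half-lives of commonly used ACEi and ARB".

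**Effect of these drugs on fibrosis (section 1).** ACEi and ARB "have been shown to regress myocardial fibrosis on biopsy".

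**Time allowed for change (section 2.2).** "The treatment duration is 52 weeks". Baseline CMR is at week 0, after the washout, and is repeated at week 52 (Table 2).

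**Allocation (section 2.2).** "Participants are randomized on an allocation ratio of 1:1", by sequentially numbered envelopes. The article neither names a stratification factor nor says that there is none.

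**Data on prior use (Table 2).** "Collection of past medical history, including medications" takes place once, at the washout visit or visit 1.

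**Analysis (section 2.4.2).** Changes in CMR endpoints are compared by Student's t-test, or by the Mann–Whitney U test if normality fails. If significant baseline differences appear, the methods may be modified to adjust for them.

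**The concern.** The half-life argument concerns the drug in the body, whereas the primary endpoint is interstitial volume. By the article's own account ACEi and ARB reduce myocardial fibrosis, and the trial allows a year for treatments to change it. It is therefore unlikely that two weeks off treatment returns a prior user's myocardium to an untreated state, and the word eliminate is too strong for this endpoint.

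The enrolled population is also mixed. Table 1 admits newly diagnosed to resistant hypertension on at least one drug, and only those on an ACEi or ARB are washed out. Prior users allocated valsartan resume RAAS blockade; other participants may be starting it. Prior use is thus a plausible predictor of the 52-week change.

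Two things are at stake in a trial of this size. Unmodelled variation widens the confidence interval, and a chance imbalance in prior use can shift the estimate in the one trial that is run. The rule in section 2.4.2 is the wrong tool for either. It lets a significance test on baseline data decide whether to adjust, and it leaves the decision discretionary even then.

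**Working it through.** **1. Reproduce the planned sample size.** Inputs from section 2.4.1: difference 3.5 mL/m², SD 5.8 mL/m², correlation 0.60, two-sided 5%, 80% power, 35 per group. Reading 5.8 as the SD at a single time point, equal at both times:

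- SD of change = 5.8 × √(2 × (1 − 0.60)) = 5.19
- n per group = 2 × (5.19 × (1.96 + 0.84) / 3.5)² = 34.5, rounded up to 35
- SE at 35 per group = 5.19 × √(2/35) = 1.24, so power = Φ(3.5/1.24 − 1.96) = 80.6%

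The plan's figure is reproduced. It corresponds to an unadjusted comparison of change scores. With the t distribution, power at 35 is 79.5%.

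**2. Gain from baseline interstitial volume.** With the same inputs:

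- Residual SD = 5.8 × √(1 − 0.60²) = 4.64
- SE = 4.64 × √(2/35) = 1.11, so power = Φ(3.5/1.11 − 1.96) = 88%
- n for 80% power = 27.6, rounded up to 28 per group

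**3. Gain from prior ACEi/ARB use.** The article gives neither the proportion of prior users (p) nor the difference in mean change between users and non-users (g). I assume p = 0.3 to 0.9 and g = 1 to 3.5 mL/m².

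- Share of change variance explained = g² p(1 − p) / 5.19²; residual SD = 5.19 × √(1 − share)
- 95% chance imbalance = 1.96 × √(2p(1 − p)/35); resulting shift in the unadjusted estimate = g × imbalance

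| p | g (mL/m²) | Variance share | Power at 35 per group | 95% imbalance (points) | Shift (mL/m²) |
|---|---|---|---|---|---|
| 0.9 | 1 | 0.3% | 80.7% | 14.1 | 0.14 |
| 0.7 | 2 | 3.1% | 81.8% | 21.5 | 0.43 |
| 0.5 | 2 | 3.7% | 82.0% | 23.4 | 0.47 |
| 0.5 | 3.5 | 11.4% | 85.0% | 23.4 | 0.82 |

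The first and last rows are the extremes of the range. The shift is 4% to 23% of the 3.5 target, or 0.11 to 0.66 of the standard error of 1.24. These gains are measured against the unadjusted change. The increment over a model that already contains baseline volume was not estimated.

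**4. Does leaving prior use out bias the test?** The unadjusted t-test was simulated with no treatment effect, 35 per group, 40,000 trials per setting, for (p, g) = (0.5, 2), (0.7, 2) and (0.5, 3.5). Type I error was 5.1%, 5.0% and 4.9%, and the mean estimate was within 0.01 mL/m² of zero.

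**5. How well does the baseline trigger work?** At 35 per group, with the chi-square test named in section 2.4.2:

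- If the underlying proportions differed by 20 points, power = Φ((0.20 − 1.96 × SE₀)/SE₁). For 40% against 60%, SE₀ = 0.1195 and SE₁ = 0.1171, giving 38%. For 60% against 80%, SE₀ = 0.1095 and SE₁ = 0.1069, giving 45%.
- Under randomization there is no underlying difference, so the observed split is the more direct case. An observed 14/35 against 21/35 gives χ² = 2.80, p = 0.09; 21/35 against 28/35 gives χ² = 3.33, p = 0.07. Neither reaches 5%.

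The trigger therefore misses imbalances of the size that chance commonly produces.

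**The case against.** **Randomization, not the washout, protects the comparison.** A reader might infer that residual effects of prior treatment confound the trial. The article does not support that. Allocation is randomized, each participant's starting fibrosis is measured after the washout, and the simulation shows neither bias nor excess type I error. Chance imbalance is already reflected in the standard error. This stands, and it limits the point to precision and to the credibility of the single estimate.

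**The washout sentence can be read narrowly.** Effects of RAAS suppression may mean current drug activity, which half-lives do address, and other ARNi studies are cited as well. The article never says that earlier structural change is reversed, and it gives no data on how quickly fibrosis returns. Persistence is therefore an inference from the article's own statements. This stands as a reason to call the wording too strong rather than wrong.

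**Covariates and stratification are often left to the SAP or full protocol.** A reader might infer that allocation is unstratified, or that the analysis disregards prior use. Neither follows. The article does not describe allocation as simple, and section 2.4.2 permits adjustment. Silence on a covariate is not a fault here. The criticism is of what section 2.4.2 does state: a conditional, discretionary rule. The abstract says endpoints are analysed with reference to baseline, but that fits a change score as well as an adjusted model.

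**The effect of prior use is assumed and small.** This stands. A g of 2 to 3 mL/m² would already be 57% to 86% of the whole target difference, a yes/no variable pools recent and long-term users, and baseline volume may absorb part of the effect.

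**Conclusion.** The point holds as a minor one. The washout rationale establishes drug clearance and should claim no more for a tissue endpoint. The comparison of arms remains valid as designed. The weakness is the unadjusted primary comparison combined with an optional adjustment rule that depends on baseline significance.

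Most of the benefit of a pre-specified model comes from baseline interstitial volume: about 81% to 88% power at 35 per group, given the plan's SD and correlation and equal SDs at both times. Prior ACEi/ARB use contributes roughly 0 to 4 power points before baseline adjustment and probably less after it. That range rests entirely on assumed prevalence and effect. Its main value is that a plausible prognostic factor is handled by a rule fixed in advance, which matters more in an open-label trial. The planned sample size does not need to change.

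**What to change.** - **Section 2.4.2:** replace the rule based on significant baseline differences with a pre-specified primary ANCOVA of the 52-week change in interstitial volume. Include treatment, baseline interstitial volume and ACEi/ARB use at enrolment (yes/no), whatever the observed balance. Show the treatment effect by prior use descriptively, without a claim of subgroup effect.
- **Section 2.2:** limit the stated purpose of the washout to removing drug activity, and say that differences in prior treatment are handled in the analysis. The washout itself is not in question.

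If an SAP already specifies such a model, aligning section 2.4.2 with it is enough.

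The cost is two degrees of freedom and a few sentences. Medication history, baseline CMR and week-52 CMR are already scheduled, so no new data or participants are needed. The change should be made before any outcome data are compared by arm.

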**Figure 1 F1:**
[figure not shown]
Recruitment, randomization, and treatment protocol. ACEi, angiotensin-converting enzyme inhibitor; ARB, angiotensin II receptor blocker; LV, left ventricular; LVH, left ventricular hypertrophy; Δ, change.

Participants are randomized on an allocation ratio of 1:1 to either sacubitril/valsartan or valsartan without blinding. Randomization service is provided by the Singapore Clinical Research Institute (SCRI) in closed, opaque, and sequentially numbered envelopes. Research member who measures CMR endpoints is blinded to treatment allocation and clinical details including blood pressure values.

The treatment duration is 52 weeks, with the same target systolic blood pressure for both treatment groups which is less than 140 mmHg according to contemporary guidelines at the time of study conception (21, 22). The initial dosage of sacubitril/valsartan is 100 mg–200 mg/day and can be titrated up to a maximum dose of 400 mg/day. The initial dosage of valsartan is 80 mg–160 mg/day and can be titrated to a maximum dose of 320 mg/day. Medications are titrated to the maximum dose tolerated by the participants. If the study medications are inadequate for optimal blood pressure control, additional non-RAAS inhibiting anti-hypertensive agents are prescribed. Study medications are dispensed by a pharmacist at NHCS. Treatment compliance is monitored by pill counting at each clinic visit.

Participants may withdraw from the study at any time. Withdrawal can be initiated and documented by the investigator if continuation would be detrimental to the participant’s well-being. If withdrawal happens after more than 12 weeks of randomized treatment, all endpoint investigations will be performed at the time of withdrawal (unless participant is not contactable, refused, or deceased). The first participant was recruited on 19 June 2019.

